### Methods in analysis to handle protocol non-adherence and any statistical method to handle missing data {20c}

For patients that do not have a valid T2EL assessment at Visit 4 (12 months, including patients who died unrelated to the index procedure), the result of the 6-month evaluation will be imputed. A multiple imputation approach will be performed to impute missing values of participants with missing assessments at Visit 3 and Visit 4 (6 months and 12 months after index procedure, including patients who died unrelated to the index procedure before Visit 3). Age, sex, and study group will be considered in the imputation approach.

### Plans to give access to the full protocol, participant level-data, and statistical code {31}

The full protocol, datasets collected during the current study, and the statistical code will be available from the corresponding author on reasonable request.

## Oversight and monitoring

### Composition of the coordinating centre and trial steering committee {5d}

The trial steering committee consists of the study leader, the statistician, and two senior physicians who have been strongly involved in conception and execution of the study. While the steering committee is meeting approximately every 4 weeks, the team running the trial day to day (one of both above-mentioned two senior physicians together with one junior physician and a study nurse) are meeting every other day and always if required.

### Composition of the data monitoring committee and its role and reporting structure {21a}

Monitoring activities are performed by monitors of the MSZ to ensure that the study is conducted in accordance with the protocol and ethical requirements. A monitoring plan describing the scope of the monitoring activities in detail will be prepared.

The monitor will have access to patient records, any information needed to verify the entries in the eCRF, and all necessary information and essential study documents. The investigator will cooperate with the monitor to ensure that any problems detected in the course of these monitoring visits are resolved. A monitoring visit report will be prepared for each visit describing the progress of the study and all identified problems.

### Adverse event reporting and harms {22}

All adverse events and severe adverse events (SAE) must be documented in the eCRF. SAEs have to be documented within 24 h. Adverse events and SAEs (including information on severity, seriousness, start and stop date) are reported immediately to the responsible monitor of the study centre by an automatically generated email.

### Risks

SE in the intervention group will be conducted during the standard EVAR procedure according to standard techniques.

The procedure itself requires insertion of a slightly oversized sheath or puncture with an additional 4F sheath. Depending on the device, standard EVAR usually requires a 14–16F access to implant the contralateral limb. Access site closure is routinely achieved using arterial closure devices certified for this procedure. The device used should be approved for closure of large bore arterial access up to 21F (26F outer diameter). A retrospective analysis of patients in the Italian Percutaneous EVAR (IPER) registry did not show a significant association between > 18F access and technical failure of percutaneous access [29]. Equally, a retrospective study on 266 patients undergoing percutaneous EVAR using the ProGlide™ system did not show an association between sheath size and groin complications [30]. In conclusion, the totality of the available evidence suggests the sheath size seems not to be associated with a significant elevation of access site complications. Therefore, we estimate the additional access-related risk for patients undergoing SE in the EVAR-SE study to be negligible.

In our experience, there have been rare cases of coil displacement into the iliac artery. In all cases, it was possible to remove the coil by endovascular means not leaving foreign material in the blood stream.

The SE procedure was shown to be associated with a 7–18 min increased operating time [17]. As the whole operation is performed percutaneously without open surgical access, the additional operating time is not expected to be associated with a higher rate of surgical site infections.

Furthermore, SE is accompanied by an additional 2–7 min of fluoroscopy time [17]. However, it was shown that the body irradiation dose was not significantly increased compared to EVAR alone [25]. The SE procedure usually is not associated with additional use of contrast media.

### Frequency and plans for auditing trial conduct {23}

An independent SMB was established. The underlying principles for the SMB are ethical and safety aspects. The SMB examines whether the conduct of the study is still ethically justifiable and whether safety of the patients is ensured. For this, the SMB is informed regularly about patient recruitment and observed safety events. Serious adverse events (SAE) are recorded on a study-specific safety form within the study database. SAE documentation is processed in written form to the SMB and the ethics committees.

### Termination criteria

Individual patient criteria resulting in termination of the study involve indications for explantation of the endograft (e.g. endoleak type I, graft infection), adverse events that make adherence to follow up unacceptable, severe kidney injury or allergic reactions to contrast media, and withdrawal of consent.

The study may be terminated in the respective study centre in case of insufficient patient recruitment, major protocol violations, or noncompliance with study requirements.

In the event of safety concerns, failure of a relevant number of recruitment centres to comply with the protocol, or inadequate recruitment of subjects, the whole trial may be terminated.

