### Sample size {14}

The primary aim is to reduce the proportion of T2EL in high-risk patients 12 months after the index procedure. The T2EL proportion in the control group after 1 year is assumed to be 45%. This assumption is based on a retrospective analysis of 100 consecutive patients treated at Klinikum rechts der Isar. The expected proportion of T2EL in the intervention group is 15%. This translates to an odds ratio of 0.22. The expected T2EL rates after 12 months in the respective groups are in accordance with the above mentioned RCT (41% vs. 14%; adjusted *OR* 0.19; 95% *CI* 0.05–0.71) [25].

Under these assumptions, 42 patients per group (84 overall) will be needed to detect a difference between the treatment groups with a statistical power of 80% (two-sided continuity-corrected chi-squared test, *α* = 5%). Due to potential loss to FU or incomplete FU, a total number of 50 patients per group is planned to be allocated to the study. Sample size calculation was performed using the software nQuery Advisor 7.0.

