## Statistical methods

### Statistical methods for primary and secondary outcomes {20a}

Primary analysis will be performed following the intention-to-treat (ITT) principle, so each participant will be analyzed in the group he or she was randomized to. Absolute and relative frequencies will be determined for the primary endpoint (T2EL 12 months after index procedure) for both study groups. For patients that do not have a valid T2EL assessment at Visit 4 (12 months, including patients who died unrelated to the index procedure), the result of the 6-month evaluation will be imputed. A multiple imputation approach will be performed to impute missing values of participants with missing assessments at Visit 3 and Visit 4 (6 months and 12 months after index procedure, including patients who died unrelated to the index procedure before Visit 3). Age, sex, and study group will be considered in the imputation approach. Logistic regression models with the presence of T2EL at 12 months as dependent variable and study group, age, and sex as independent variables will be fitted to the imputed datasets. Results will be aggregated following Rubin’s rules, and an odds ratio with corresponding 95% confidence interval will be estimated and presented. Due to the small number of expected events, study centre will not be included as independent variable in the model. Sensitivity analyses based on complete cases only and on a per protocol set including only patients that were treated as described in the surgery SOP for their allocated study group will be conducted. Additionally, a time-to-event analysis considering death as competing event will be performed as sensitivity analysis.

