### Withdrawals

Patients who wish to withdraw from the study may do so at any point. In this case, no further data will be collected, while already collected data might need to be discarded upon the patient’s wish. Withdrawn participants will be replaced in order to reach the projected sample size.

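### Study participation ends at an indication for explantation, so later endpoint events can go unobserved; replacing withdrawn patients is redundant and conflicts with ITT if the originals are dropped

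*Protocol article*

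**What the plan says.** All references are to the protocol article.

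- **Termination criteria.** "Individual patient criteria resulting in termination of the study involve indications for explantation of the endograft (e.g. endoleak type I, graft infection". The same sentence adds adverse events that make continued follow-up untenable, severe kidney injury, contrast allergy and withdrawal of consent. It does not say whether any data are collected afterwards.
- **Withdrawals.** For patients who wish to withdraw, data collection stops and existing data may have to be discarded at their request. Then: "Withdrawn participants will be replaced in order to reach the projected sample size".
- **Secondary endpoints.** These include any re-intervention (endoleak and graft infection are among the named reasons), type I/III endoleak, rupture and mortality at 12 months, and the change in SF-36 to 12 months.
- **Statistical methods {20a} and {20c}.** "Primary analysis will be performed following the intention-to-treat (ITT) principle", with each participant kept in the randomised group. A missing 12-month T2EL result takes the 6-month value. If both are missing, it is multiply imputed using age, sex and study group. Re-intervention, type I/III endoleak, rupture and death are analysed as times to event.
- **Sample size {14}.** "42 patients per group (84 overall) will be needed to detect a difference between the treatment groups with a statistical power of 80" per cent. "Due to potential loss to FU or incomplete FU, a total number of 50 patients per group is planned to be allocated".

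**The concern.** The individual stopping rule is tied to the course of the disease and the device. A patient reaches it because the repair is failing or because of harm, and that is when the secondary endpoints become most informative. If observation stops there, the most serious re-intervention and anything after it may never enter the database. The Kaplan-Meier and log-rank analyses would treat that patient as having the same future risk as patients still under observation. Safety of sac embolization is a stated secondary objective, and treatment is open to patients and operators, so such losses could differ between arms.

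The replacement sentence is a second and separate matter. It suggests that a withdrawn patient no longer counts towards the projected sample, which sits badly with a promise to analyse everyone as randomised.

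**Working it through.** **1. Order of events.** The trigger is the *indication* for explantation, so it comes before the operation. The Background lists conversion to open repair among the re-interventions after EVAR, and the Secondary endpoints count re-intervention for endoleak and graft infection. Setting rule and endpoints side by side:

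- Type I endoleak or infection that leads to the indication: seen before termination, therefore recorded.
- The explantation itself: after the trigger, can be missed.
- Rupture, death and SF-36 at 12 months: after the trigger, can be missed.
- Renal function at the 12-month visit (Table 1): can be missed in the patients terminated for severe kidney injury.

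**2. What the analysis does with these patients.**

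- Time-to-event endpoints: they are censored at termination, for a reason linked to their prognosis.
- Primary endpoint: the 6-month T2EL result is carried forward if it exists. Otherwise T2EL is imputed from age, sex and group. Sections {20a} and {20c} name deaths unrelated to the procedure but give no rule for termination because of explantation or harm. A patient without the graft would be given a T2EL status as if it were still in place.

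**3. The sample size and its allowance.** Inputs from Sample size {14}: "The T2EL proportion in the control group after 1 year is assumed to be 45" per cent; "The expected proportion of T2EL in the intervention group is 15" per cent; "two-sided continuity-corrected chi-squared test, *α* = 5" per cent; power 80%.

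- Uncorrected: n = [1.960·√(2·0.30·0.70) + 0.842·√(0.45·0.55 + 0.15·0.85)]² / 0.30² = (1.270 + 0.515)² / 0.09 ≈ 35.4.
- Continuity-corrected: n = (35.4/4)·[1 + √(1 + 4/(35.4·0.30))]² ≈ 41.8, so **42 per group**. The plan's figure is reproduced.
- Allowance: (50 − 42)/50 = **16%**.
- Exact power of the corrected test: 80.5% at 42 per group and 88.7% at 50 per group.

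The target power is therefore kept with up to 8 losses per group and no replacement.

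**4. Possible size for the primary endpoint.** The documents give no termination rate. Assume k of 50 embolization patients have no 12-month result and 15% of the remaining 50 − k have T2EL. The true proportion then lies between 0.15·(50 − k)/50 (none of the k has T2EL) and [0.15·(50 − k) + k]/50 (all have it):

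- k = 1: 14.7% to 16.7%
- k = 3: 14.1% to 20.1%
- k = 5: 13.5% to 23.5%
- k = 8: 12.6% to 28.6%

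These are extreme bounds, not estimates, and they ignore what a 6-month result would tell. Recruiting replacements restores the count but does not narrow them, because the missing patients are selected by outcome.

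**5. Possible size for rare endpoints.** One unobserved event in an arm of 50 shifts a crude proportion by 1/50 = 2 percentage points. The Background cites 1% mortality after elective EVAR, or about 1 death in 100 patients. That figure is not a rate of explantation or rupture, but it shows how few events such a comparison may rest on.

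**The case against.** Several stronger readings are tempting, and the documents do not support them.

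- *Every type I endoleak or serious harm ends participation.* No. The criterion is an indication for explantation, with type I endoleak as an example, and the harm criteria are specific.
- *The trial deletes the endpoint events that trigger termination.* No. The trigger must be detected first. Endoleak, re-intervention and adverse events are recorded at visits, all adverse events go into the eCRF, and nothing says that these entries are removed.
- *Patients with bad outcomes are swapped for new ones.* Not stated. Replacement and the stop of data collection are written for patients who wish to withdraw. Whether patients terminated on other grounds are treated alike is left open.
- *Replaced patients vanish from the denominators.* With 5 replaced per arm one could compute 10/110 = 9.1%, but no sentence takes them out of the ITT set, and the 5 is an invention. Replacement alone only raises the number randomised.

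It can also be said that secondary endpoints are exploratory, that little effect on 12-month mortality is expected, that cumulative incidence functions are foreseen where competing risks exist, and that the full protocol, which is not shown, may describe contact after termination. All of that is fair and limits the weight of the point. It does not remove it. Coding explantation as a competing event requires that it be observed, and no analysis plan recovers data that were not collected. The article states the termination rule without separating it from the end of follow-up.

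**Conclusion.** The point holds in a limited form. As worded, the Termination criteria allow outcome-dependent loss of what follows the trigger: explantation, rupture, death and month-12 SF-36. The censoring and imputation rules do not deal with that loss. The replacement sentence is redundant within the 16% allowance, and it contradicts the ITT commitment only if the original patients are dropped.

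The stated sample size is correct and does not change. The size of any bias cannot be computed, because neither a termination nor a withdrawal rate is given. The ranges above rest on an assumed 1 to 8 patients without a 12-month result in an arm of 50. The effect on T2EL is probably smaller than on the rare safety endpoints. The conclusion assumes that the full protocol does not already provide for follow-up after termination. If it does, the remaining task is to say so and to settle the replacement sentence.

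**What to change.** Reconcile Secondary endpoints, Statistical methods {20a}/{20c}, Termination criteria and Withdrawals by amendment:

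1. State that meeting an individual termination criterion other than withdrawal of consent does not end data collection for re-intervention (including explantation), rupture, vital status and SF-36 up to month 12.
2. Delete the replacement sentence. The 8 extra patients per group cover losses.
3. State that every randomised patient stays in the ITT set with the data that consent allows. Data discarded at a patient's request cannot be used.
4. State how the 12-month T2EL status is handled once the graft has been removed.

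This concerns data collection and analysis only. Clinical decisions, including whether contrast imaging continues, stay as they are. The cost is an amendment and a few extra contacts, at visits that the article describes as following clinical routine. The number of patients does not change.

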### Withdrawals

Patients who wish to withdraw from the study may do so at any point. In this case, no further data will be collected, while already collected data might need to be discarded upon the patient’s wish. Withdrawn participants will be replaced in order to reach the projected sample size.

### Registration

The EVAR-SE study was registered on the ClinicalTrials.gov public website on 23 December 2022. The ClinicalTrials.gov identifier is NCT05665101.

### Plans for communicating important protocol amendments to relevant parties (e.g. trial participants, ethics committees) {25}

All relevant protocol amendments will be communicated to the ethics committees of the participating centres, ClinicalTrials.gov, and the journal in which the study protocol was publishes.

### Dissemination plans {31a}

The study protocol hereby is published in a peer-reviewed scientific journal. Study results will be prepared for publication in a reputable peer-reviewed scientific journal in accordance with the CONSORT statement [31]. Further, results will be disseminated in lay language to patients and public society. The BMBF will be acknowledged as funder in all publications and presentations by providing the BMBF project number 01KG2128.

### Good clinical practice

The study is carried out in accordance with the principles of the Declaration of Helsinki by the World Medical Association and specific applicable national ethical and regulatory requirements [“Berufsordnung für Ärzte”, General Data Protection Regulation (GDPR)] [32]. Moreover, an independent SMB is established.

## Discussion

The short-term outcome of standard EVAR, with in-hospital mortality rates of less than 1% and low rates of primary complications, makes EVAR the first-choice treatment for patients and surgeons alike. The long-term success of the treatment is, however, endangered by T2EL, which occur in one out of four patients. By identifying patients at higher risk of T2EL and taking sac embolization as preventive measure, the incidence of T2EL including their potential complications might be reduced.

Sac embolization has shown encouraging results in other studies [17], especially the recently published randomized SCOPE trial [25]. This might lead to the question why a further exploratory study is necessary before conducting a confirmatory study with long-term follow up (5–10 years) and aneurysm-related survival as primary endpoint. All previous studies hold major drawbacks that we are planning to overcome with EVAR-SE:

### Primary endpoint

The conductors of SCOPE admit as major limitation that the primary endpoint should have been uniform for all patients, rather than at different timelines (1, 6, 12, and 24 months) [25]. The primary endpoint for EVAR-SE will be the T2EL proportion of the intervention group as compared to the control group at 12 months after EVAR treatment, as only very few endoleaks occur or seal at a later time point.

### Choice of coils should not be limited to one medical product

Previous RCTs comparing EVAR with SE to standard EVAR allowed only for predefined coil manufacturers [22, 25]. The aim of EVAR-SE is to evaluate the SE method in an easily convertible setting. We therefore plan to allow for CE-certified coils from various industrial manufacturers.

### CEUS as primary follow up imaging

For the SCOPE trial — similar to other earlier studies — patients received at least five CTAs within 2 years (routine planning CTA for EVAR, further scans at 1, 6, 12, and 24 months), combined with color-Doppler ultrasound. For EVAR-SE, a contemporary follow-up protocol will be implemented, replacing most CTA scans by CEUS. Patients will be exposed to less radiation and iodine contrast agent (comparable or less than routine care conditions). CEUS, when compared to CTA, has already been proven to be as sensitive in detecting endoleaks, especially T2EL [33]. It can also detect delayed late T2EL, possibly missed by CTA [34]. CEUS also performs markedly better in detecting endoleaks compared to color-Doppler ultrasound [35]. Thus, CEUS is currently recommended as primary imaging method after EVAR, while CTA should only be performed in the presence of sac enlargement or endoleak [36]. In the special situation, after SE, currently, there is no published data on the use of CEUS as FU imaging. CTA, however, can be hard to interpret, as the implanted coils are causing artefacts [25]. In our own experience, CEUS works well when scanning aneurysm sacs after SE and might help to overcome this issue.

### Adherence to follow-up

Many patients did not attend planned follow-up examinations in SCOPE for unknown reasons [25]. For EVAR-SE, we conducted a patient survey with promising results regarding adherence to follow-up protocols.

### Patient relevant outcome measures

Earlier studies lacked patient relevant outcomes, while EVAR-SE will include quality of life as secondary outcome measure.

### Evaluation in CTA by independent core lab

An independent core lab, consisting of a vascular surgeon and a radiologist (both otherwise not involved in the conduct of the study), will be implemented. The core lab will evaluate pseudonymized CTA scans (before EVAR and after 12 months).

In summary, the method, as applied in EVAR-SE, is technically easy and potentially applicable for everyday use. Thus, if proven efficient, it might find wide acceptance in clinical practice and will be relevant for future AAA treatment guidelines.

## Current trial status

The latest protocol version (number 1.1; 24.11.2022) was approved by the domestic Ethics Committee of the Technical University of Munich in December 2022 and all other ethics committees of the respective study sites (respective reference numbers see below).

Initiation was completed at Klinikum rechts der Isar of the Technical University of Munich in December 2022, at St. Joseph’s Hospital Wiesbaden in June 2023, at the University Hospital Dresden in August 2023, and at the University Hospital Augsburg in September 2023.

The first patient was recruited on 13th January 2023. Until today (1st October 2023), a total of 19 patients have been randomized. Recruitment is estimated to be complete in the 1st quarter of 2025.

